- **Study Protocol**
- **Effectiveness of Reciproc system for anterior teeth with apical periodontitis: a randomized controlled pragmatic trial**
- **Proponent:**
- PhD Student: [name]
- Health Sciences Graduate Program
- Federal University of Sergipe
- **Doctoral Adviser:**
- [name]. [name]
- Department of Dentistry
- Health Campus / Biology and Health Science Center
- Federal University of Sergipe
- Aracaju
- June 2015
- **ABSTRACT**
- Single file canal preparation techniques emerged in an attempt to overcome drawbacks related to manual and continuous rotary techniques. It has shown promising results in in-vitro studies, but its effectiveness has not yet been tested in clinical studies. Hence, this proposal seeks to investigate, through an equivalency randomized controlled clinical trial, the effectiveness of the Reciproc® single file, single cone system, regarding its success rate, incidence rate of post-operative pain and PAI score changes. This trial will follow the Consort guidelines, having a parallel design and using an active treatment as control – the crown-down instrumentation technique and the lateral condensation obturation technique. Patients in need of endodontic treatment for anterior teeth due to pulp necrosis and with radiographic evidence of apical periodontitis will be randomized to receive endodontic treatment either by the Reciproc® single file, single cone system or by the crown-down manual technique with stainless steel files. Patients will be questioned about their pain levels at baseline and then 24 hours, 72 hours days and 7 days after treatment is performed. The Wilcoxon test will be used to compare treatment pain scores. Patients will be called for one- year follow-up visits in which PAI score changes and clinical signs of periapical pathosis will be ascertained. Data related to PAI scores will be submitted to the Wilcoxon test to compare treatment outcomes and to the Man-Whitney test to compare one-year follow-up scores within each treatment group. Each individual treatment will be classified as “success” if their PAI scores are 2 or lower and they show no clinical signs or symptoms of periapical disease. Success rates of each treatment and the relative risk of experimental group in relation to control will be determined. In addition, Fishers exact test will be used to compare treatment groups’ success rates. For all analyses, a 95% significance level will be used.
- **Key Words:** Periapical Periodontitis; Root Canal therapy; Randomized Controlled Clinical Trial
- **RESUMO**
- A técnica de instrumentação de canais radiculares com único instrumento reciprocante surgiu como uma tentativa de superar as limitações apresentadas pelas técnicas manuais e de rotação continua. Apesar da facilidade técnica, poucos estudos avaliaram a efetividade do uso de instrumentação reciprocante na prática clínica. Assim, o objetivo desta proposta será avaliar o desempenho clínico da instrumentação reciprocante e obturação com cone único do sistema Reciproc®, no que concerne ao índice de sucesso do tratamento endodôntico e à incidência de dor pós-operatória, através de um ensaio clínico randomizado controlado. Este será realizado seguindo as recomendações do *Consort*, usando controle ativo – instrumentação manual pela técnica coroa-ápice e obturação pela técnica da condensação lateral. Pacientes que apresentem dentes anteriores com quadro clínico de necrose pulpar e evidência radiográfica de periodontite apical serão randomizados para tratamento endodôntico com limas do sistema Reciproc® ou para tratamento com limas manuais. O paciente será questionado qual seu nível de dor percebida antes de iniciar o tratamento e 24 horas, 72 horas e 7 dias após sua realização; os escores serão submetidos ao teste de Wilcoxon para comparação das técnicas endodônticas. Doze meses após o tratamento, os pacientes serão convocados para nova avaliação clinica e radiográfica, na qual serão verificadas alterações no índice PAI com relação ao registrado no *baseline* e sinais ou sintomas clínicos de periodontite periapical. Os dados relativos ao índice PAI serão submetidos ao teste de Wilcoxon para comparação entre as técnicas e ao teste de Man-Whitney para comparar os scores observados na avaliação de 12 meses. O sucesso de cada tratamento será caracterizado se o dente apresentar índice PAI igual ou inferior a 2 e na ausência de sintomatologia clínica. As percentagens de sucesso de cada tratamento e o risco relativo do tratamento experimental em relação ao controle serão calculados. Além disso, as percentagens de sucesso de cada tratamento serão comparadas pelo teste exato de Fisher. Para todas as análises, será utilizado nível de significância estatística de 95%.
- **Palavras-chave:** Periodontite Periapical; Preparo de Canal Radicular; Ensaio Clínico
- **1. Introduction**
- 1.1 Research problem
- One of the main objectives of endodontic therapy is to treat the inflammation of the periapical tissues that is caused by the presence of microbes in the root canal system (RCS) (1). To achieve this objective, the RCS must be disinfected, which is only possible through the cleaning and shaping of the canal with endodontic files and irrigant solutions with antimicrobial properties (2). Traditionally, cleaning and shaping procedures are performed with stainless steel hand files. However, these files have low flexibility, which can result in alteration of root canal anatomy - especially in curved canals (3) - which is not desirable.
- To overcome this problem, nickel titanium files, which present the property of superelasticity, began to be used in rotary motion for root canal preparation. This manner of preparing canals reduces treatment time and the clinicians’ stress, which makes root canal preparation safer and more efficient. However, the main disadvantages of the rotary technique with NiTi files are the high possibility of file separation in the root canal and the necessity of multiple sequences of files to shape the RCS (4,5).
- In an attempt to simplify the root canal preparation phase and reduce the incidence of file breakage, researchers began to the study the preparation efficacy of a single NiTi file in reciprocating motion. The result was the development of the “single-file instrumentation technique”, in which the rotary motion was replaced by the reciprocating motion, mainly to reduce the risk of file breakage (6).
- However, even though it has the advantage of simplicity, the clinical effectiveness and efficacy of the reciprocating single file technique has been poorly studied. Furthermore, results from laboratory studies have raised concern about the technique. First, because it is a very fast technique to execute, reciprocating root canal preparation may hamper the antimicrobial efficacy of the irrigation solution, which is time dependent. Second, recent studies have demonstrated that debris extrusion through the apex foramen related to the reciprocating single file technique is higher than that observed in other techniques (7,8), which may result in higher incidence and severity of post-operative pain.

- 1.2 State of the art
- [name] developed the first reciprocating single file system – the Reciproc system. According to him, the main advantage of the system has is that a single file is required to shape the canal, which makes the technique easy and simple to execute and reduces the risk of cross-contamination (9,10). Furthermore, he also claims that the system presents a lower risk of file breakage. Indeed, many laboratory studies have shown that reciprocating motion enhances the cyclic fatigue resistance of NiTi files, and that reciprocating systems reduce treatment time (11,12,13). However, other laboratory studies have reported that the antibacterial efficacy of reciprocating systems is not superior to that of other systems (14) and that their use may result in a higher extrusion of debris through the apical foramen (7), which can increase the incidence and severity of postoperative pain. This has already been observed in some clinical studies (15, 16). It is important to point out that extrusion of debris through the apex is still a controversial matter (17).
- To the best of our knowledge, there are no controlled clinical studies evaluating the long-term outcomes of endodontic treatment performed with reciprocating single file systems. We found one single study that reported a 93% treatment success rate after reciprocating single file root canal preparation of teeth with apical periodontitis after a period of follow-up of three years. However, this study lacked a control group and was conducted and written by the developer of the system. (18).
- 1.3 Proposal Identification
- This proposal seeks, through a randomized controlled trial, to evaluate the clinical performance of reciprocating single file root canal preparation concerning postoperative pain and the healing of apical lesions.
- **2. Justification**
- A decrease in treatment time may enable a reduction in the cost of treatment, while increasing the productivity of public and private clinics. In addition, it also enhances ergonomics and makes the experience of root canal treatment less uncomfortable for patients. Despite these advantages, faster root canal preparation techniques must not compromise the short and long-term outcomes of root canal treatment. The reciprocating single file philosophy was developed to reduce and simplify root canal treatment time. If its clinical performance is similar or better than the performance of other root canal preparation techniques, it will enhance services delivered to the public, reducing costs and enhancing productivity. Hence, it is important to investigate the clinical performance of endodontic techniques that make use of reciprocating single file root canal preparation in order to help private and public endodontic treatment providers to chose and manage their practice.
- **3. Research Objectives**
- 3.1- General objective
- To evaluate the clinical effectiveness of the Reciproc reciprocating single file system in regards to the treatment of anterior teeth with apical periodontitis
- 3.2. – Specific objectives

1. Compare mean periapical index score (PAI) score changes between reciprocating single file and hand file instrumentation of root canals;
2. Compare the success rate of treatments performed with reciprocating single file and hand file instrumentation of root canals;
3. Compare the incidence and severity of postoperative pain between the two instrumentation modalities;
4. Compare the incidence of flair-up between the two instrumentation modalities

- **4. Goals**

1. Contribute to enhance the scientific knowledge related to the preparation and obturation of root canals with reciprocating single files and the single cone technique, respectively.
2. Contribute to enhance the quality of care offered by public clinics in which endodontic treatment is performed
3. Improve the quality of dentistry-related clinical trials of the post graduate program in Health Sciences of the Federal University of Sergipe, Brazil, considering that these are at the top of the scientific evidence pyramid and, hence, promote evidence based dentistry.
4. Establish partnership with other institutions for the design and execution of multicenter randomized clinical trials;
5. Enhance the quality of education provided to students of the graduate program in Health Sciences of the Federal University of Sergipe;
6. Produce a doctoral thesis and at least two original research articles to be published in journals with an impact factor of 2 or more.
7. **Methodology**

- 5.1 Experimental Design
- This study will be a randomized controlled pragmatic clinical trial, which will follow the CONSORT (<http://www.consort-statement.org/>) statement guidelines. It will have a two-arm, parallel design (1:1 allocation ratio equivalency). The endodontic treatments to be performed are either a combination of a single-file and single-cone (SFSC) technique using the Reciproc system (experimental group) or an association of the crown-down hand files with the lateral compaction obturation (HFLC) technique (control group). The main outcome of interest is mean periapical index score (PAI) (19) difference between the two groups 12 months after treatment. Peak of pain during the first 24 hours after treatment and postoperative pain 24, 48 hours and 7 days after treatment are the secondary outcomes.
- The trial will be based on the following PICO question:
- P (Population): patients above 18 years of age, who are scheduled for an endodontic treatment in one of the public services where the study was performed cities (i.e., Capela, Estância, Laranjeiras and Nossa Senhora do Socorro) located in the state of Sergipe (Brazil), with anterior teeth presenting pulp necrosis and radiographic evidence of apical periodontitis (symptomatic apical periodontitis, asymptomatic apical periodontitis, and chronic apical abscess) with a diameter greater than 2 mm.
- I (Intervention): A combination of a reciprocating single-file and single-cone technique using the Reciproc system.
- C (Control): An association of the crown-down technique hand files with the lateral compaction obturation technique.
- O (Outcomes): Mean PAI difference between the intervention and the control group 12 months after treatment.
- Therefore, the research question is the following: For patients presenting anterior teeth with pulp necrosis and apical periodontitis, is there difference in the outcomes obtained with hand file instrumentation and lateral compaction obturation compared with the outcomes obtained with reciprocating single file instrumentation and single cone obturation, concerning the healing of periapical lesions and postoperative pain incidence and severity? The hypothesis to be tested is that using reciprocating single files instrumentation and single cone obturation has similar effectiveness treating apical periodontitis as hand file instrumentation and lateral compaction obturation technique. In addition, the hypothesis that both endodontic protocols result in the same incidence and severity of postoperative pain and flair-up will also be tested.
- 5.2 Method
- 5.2.1 Sample Size Calculation
- The sample size was calculated for the main outcome, defined as the mean periapical index score (PAI) difference between protocols of the apical lesion 1 year after treatment. The calculation for similarity trial used an equivalence limit of 0.5, a standard deviation of 0.74 (20), type I error of 0.05, and a power test of 0.90. Furthermore, the sample was increased by 20% to compensate for any drop-out. This resulted in 60 teeth per experimental condition.
- 5.2.2 Recruitment and eligibility criteria
- The recruited participants will be patients who are scheduled for an endodontic treatment in one of the public services where the study will take place. Patients with anterior teeth presenting pulp necrosis and radiographic evidence of apical periodontitis (symptomatic apical periodontitis, asymptomatic apical periodontitis, and chronic apical abscess) with a diameter greater than 2 mm will be invited to participate in the study. Those who agreed to participate and sign the informed consent (appendix I) form will be included in this study. Only one tooth per participant will be included in the trial. Teeth with an immature apex, any radiographic evidence of root resorption, previously treated root canal or requiring extensive prosthetic rehabilitation will be excluded. Participants presenting a pre-existing health or oral condition that placed them at risk during the trial, as well as those having generalized periodontal disease, and women who are pregnant or breastfeeding are also going to be excluded.
- 5.2.3 Baseline evaluation
- To evaluate participants’, the pupal condition will be evaluated through thermal sensitivity tests – cold and heat – and through periapical radiographs made by the paralleling technique. A clinical evaluation will also be performed (visual inspection, palpation, vertical and horizontal percussion) to identify and register the presence or absence of sinus tract, tenderness, tooth mobility and pain.
- If the occurrence of pulpal necrosis and apical periodontitis is confirmed and if the patient gives written consent to participate in the study, the baseline PAI will be recorded according with the instructions of Orstavick et al (19).
- Table 1. Periapical Index Score (19).

| - PAI SCORE | - Criteria |
| --- | --- |
| - 1 | - Normal Periapical structures |
| - 2 | - Small changes in bone structure |
| - 3 | - Changes in bone structure with some mineral loss |
| - 4 | - Periodontitis with well-defined radiolucent area |
| - 5 | - Severe periodontitis |

- In case the patient reports any sensitivity before treatment, its level will be registered according to the verbal scale detailed in table 2. If the patient does not report any pain, the score 0 will be registered, which corresponds to absence of pain.
- Table 2. Verbal pain scale (21).

| - 5-Level pain scale to evaluate pain severity: Reference Values given to patients | | |
| --- | --- | --- |
| - 0 | - No pain | - The patient feels good |
| - 1 | - Mild pain | - If distracted, he/she does not fell pain |
| - 2 | - Moderate Pain | - The patient feels moderate pain, even when concentrating on some activity |
| - 3 | - Considerable | - The patients feel very unwell but nevertheless can continue with ordinary activities of daily life |
| - 4 | - Severe pain | - The patient is forced to give up ordinary activities of daily life |
| - 5 | - Extreme | - The patient is no longer able to perform any type of activity and needs to lie down and rest |

- 5.2.4 Random sequence generation and allocation concealment
- A random list will be created using the website [www.sealedenvelope.com](http://www.sealedenvelope.com/). The treatment to be performed on each patient will be placed into opaque and sealed envelopes by a third party not involved in the study intervention. The dentists who will perform the clinical procedures will only open the envelope at the moment of the intervention.
- 5.2.5 Study interventions
- The participants allocated to the experimental intervention group will have their treatment performed by root canal preparation with reciprocating single file (Reciproc system) and obturated with the single cone obturation technique (SFSC group). Participants allocated to experimental control group will have their teeth treated by the crown-down instrumentation technique and the lateral compaction obturation technique (HFLC group).
- 5.2.6 Treatment protocol
- The endodontic treatments will be performed by three endodontists with more than 5 years of clinical experience. After the administration of local anesthesia and the placement of a rubber dam, the carious lesion will be removed and the access cavity performed. All endodontic treatments will be performed in a single session according to the randomization procedure.
- HFLC technique: The glide path will be established with stainless steel hand K-files up to a size #15. Then, the crown-down technique will be performed, initially with Gates-Glidden burs, which are to be used in a step-down manner to enlarge the orifice, prepare the cervical and middle-thirds of the canal, and provide straight-line access to its apical third. The apical foramen will be located by using an electronic apex locator (RomiApex A-15 Romidan, Kiryat Ono, Israel), and the working length established 1.0 mm short of its “0.0” reading. Apical preparation will be performed using ISO stainless steel hand files (Dentsply Sirona Endodontics, Ballaigues, Switzerland), starting with the selection of the first file to bind at the working length. The final instrumentation file will be set at 3 sizes larger than the first file used. The lateral compaction obturation technique will be used to fill the canals. A .02 taper gutta-percha cone will be selected according to the master apical file and then prefitted into the canal at the working length. After the canal is dried with paper points (Dentsply Sirona Endodontics), the master cone will be lightly coated with an epoxy resin-based sealer (AH Plus, Dentsply DeTrey, Konstanz, Germany) and placed into the canal down to the working length. Lateral compaction will be performed with finger spreaders (Dentsply Sirona Endodontics) and accessory cones (Dentsply Sirona Endodontics) chosen according to the final root canal dimensions. The excess filling material will be removed with a heated instrument and the access cavity sealed with glass-ionomer.
- SFSC technique: Root canal preparation will be performed with Reciproc instruments (VDW GmbH, Munich, Germany), following the instructions of Yared (8). The Reciproc file selection will be based on a preoperative radiograph and root canal space. If the canal is partially or completely invisible on the radiograph, an R25 file will be selected. Otherwise, a #30 or #20 hand file will be inserted passively to 2/3 of the estimated working length. An R50 file will be selected whenever a #30 hand file reached this length, and an R40 file whenever the 2/3 are reached by a #20 hand file. R25 will be selected for narrow canals. The Reciproc instrument will be introduced into the root canal with a slow in-and-out pecking motion, which does not exceed 3-4 mm in amplitude. After three in-and-out movements, the file will be pulled out of the canals to clean the flutes. When the instrument reaches 2/3 of the estimated working length, the foramen will be located by using an electronic apex locator (RomiApex A-15), and the actual working length was established 1.0 mm short of the “0.0” electronic reading. Finally, the Reciproc instrument will then be reused in the same manner until the working length is reached. After canal preparation, a matching-taper single gutta-percha cone (VDW GmbH, Munich, Germany) will be selected according to the file used to instrument the canal. The canal will be dried with sterile paper points (Dentsply Sirona Endodontics), and the selected cone was lightly coated with AH plus sealer and placed into the canal down to the working length. The excess filling material will then be removed with a heated instrument, and the access cavities sealed with glass-ionomer.
- All teeth from both groups will be submitted to the following procedures: irrigation with 2.5% sodium hypochlorite; canal patency by passing a stainless steel K-file ≤ #15 approximately 1.0 mm beyond the working length; smear layer removal with 17% EDTA for 3 minutes; and final restoration with composite resin. Pre- and post-operative radiographs will be taken with Kodak UltraSpeed #2, D sensitivity film (Kodak, São Paulo, SP, Brazil), processed manually by the time/temperature method. The long cone parallel technique will be used by employing X-ray holders (Endo Rh plus, Indusbello, Londrina, PR, Brazil), which are to be placed on the 30.5 x 40.5 mm size film, parallel to the long axis of the tooth and perpendicular to the X-Ray.
- 5.2.8 Evaluations
- Thirty periapical radiographs of endodontically treated teeth not included in the study will be used for calibration procedures by two independent and blinded evaluators. The evaluation of such radiographs will be repeated until intra- and inter-evaluator agreement has a Kappa coefficient higher than 0.80.
- Apical periodontitis will be classified using the initial radiography, and according to PAI scores. Bitewing film holders will be used to standardize the position of radiographs. Silicone impression material (Optosil Comfort, Heraeus Kulzer, Hanau, Germany) will be placed on the film holder, and impressions of the tooth undergoing treatment will be taken. Then, the impression will be used to place the device in the same position during the follow-up evaluations.
- The patients will be called after 12-months. New periapical radiographs will be taken, and the lesions will be reclassified according to the PAI scale. Then, the teeth will be classified as healed (scores 1 or 2); healing (reduced score compared to baseline, but higher than 2); or not healed. Teeth that are clinically asymptomatic – defined by absence of pain, tenderness to percussion and/or palpation, sinus tract, or soft tissue swelling – and present a PAI score of 1 or 2 will be classified as “success”.
- If the patients record any postoperative pain, it will be recorded using both a visual analog scale (VAS) and a verbal rating scale (VRS). For the VAS, the patient will set her/his pain level by pointing (with a pen) along a 10-cm continuous line between two endpoints (ranging from the absence of pain to unbearable pain). The distance between the marking and the border corresponding to the absence of pain will be recorded. The peak of pain at the first 24 h, as well the pain reported at 24 h, 72 h and 7 days after the end of the endodontic treatment will be recorded. Postoperative pain was also scored according to the VRS. The latter scale was used to assess the incidence of postoperative pain (scores differing from 0). The occurrence of flare-up was recorded when the patients presented severe pain and swelling following the endodontic treatment.
- 5.2.8 Blinding
- Because this is an intervention study, clinicians cannot be blinded for the procedures they will perform. The patients will not be informed of which group they are allocated to.
- 5.3 Statistical analysis
- Baseline demographic data of the participants and clinical characteristics of the teeth included in the study will be categorized, and the absolute and relative frequencies calculated (except for PAI scores, final preparation size scores, age and follow-up time). The difference between the interventions regarding the distribution of these characteristics will be assessed by Chi-squared analysis. For PAI scores, final preparation size scores, age and follow-up time, data will be analyzed using either t-test or Mann-Whitney Rank-Sum test.
- The Wilcoxon Rank-Sum test for equivalence using two one-sided tests (TOST) procedure will be used to assess if, 12 months after the treatment, the 95% confidence intervals of the mean PAI score treatment difference falls within the pre-established equivalence limit (main outcome of interest). For all other outcomes, traditional two-sided superiority analyses will be used. The association between treatment protocol and changes on periapical status will be analyzed by Chi-squared test or by Fisher`s exact test. The success rates for each treatment protocol will be calculated, and differences analyzed by Chi-squared testing. Univariate logistic regression will used to determine any association between explanatory variables and the treatment’s success rate. Factors with a p-value < 0.1 will be included in a multivariate analysis. Odds ratios and 95% confidence intervals will be calculated.
- For all VAS data, normal distribution and possible differences between the treatments will be assessed through the Shapiro-Wilk test and t-test, respectively. Data from VRS will be analyzed through the Wilcoxon rank-sum test. The incidence of postoperative pain and flare-up will be calculated, and Chi-squared tests will be used to assess any possible association between treatment and incidence. Differences between the treatments regarding the incidence and intensity of postoperative pain will be calculated, as well as their confidence intervals at 95%. The level of significance will be set at 95% for all analyses.
- .
- **6. Scientific contributions of the proposal**

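### The justification asks whether Reciproc is similar or better, but the plan gives no reading for a primary interval that excludes harm and crosses only the favourable equivalence limit

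*Protocol*

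**What the plan says.** Section 2 (Justification) explains why the trial is worth doing. It holds that "faster root canal preparation techniques must not compromise the short and long-term outcomes of root canal treatment", and then: "If its clinical performance is similar or better than the performance of other root canal preparation techniques, it will enhance services delivered to the public". Both statements point one way: the technique loses its case only if it is worse.

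The operative sections are framed differently. Section 5.1 calls the design an equivalency trial and asks a question without direction, "is there difference in the outcomes obtained with hand file instrumentation and lateral compaction obturation compared with the outcomes obtained with reciprocating single file instrumentation". Its hypothesis is that the reciprocating protocol "has similar effectiveness treating apical periodontitis as hand file instrumentation and lateral compaction obturation technique". The outcome is "Mean PAI difference between the intervention and the control group 12 months after treatment", with no statement of which arm is subtracted from which. Section 5.2.1 sizes the trial on an equivalence limit of 0.5, SD 0.74, type I error 0.05 and power 0.90, giving 60 teeth per arm after a 20% dropout allowance.

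Section 5.3 sets the decision rule. "The Wilcoxon Rank-Sum test for equivalence using two one-sided tests (TOST) procedure will be used", to assess whether "the 95% confidence intervals of the mean PAI score treatment difference falls within the pre-established equivalence limit". It assigns two-sided superiority tests to every outcome except this one.

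**The concern.** Take the difference as SFSC (Reciproc) minus HFLC (hand files), so that a negative value favours Reciproc; higher PAI is worse (Table 1, section 5.2.3). An interval wholly below +0.5 that extends past -0.5 rules out harm of the size the protocol treats as important. It therefore answers section 2 favourably. Under section 5.3 it only fails the equivalence criterion, and no other primary conclusion is defined for it.

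For example, with 48 evaluable teeth per arm and an observed difference of -0.30, the 95% interval is -0.30 ± 0.296, or (-0.596, -0.004). The 90% interval is -0.30 ± 0.248, or (-0.548, -0.052). Both exclude harm, both even exclude zero, and both miss equivalence.

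At stake is how such a result may be reported. If the investigators call it non-inferior or better only after seeing it, the claim is post hoc.

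**Working it through.** **Inputs.** From section 5.2.1: limit 0.5 (read as ±0.5), SD 0.74, type I error 0.05, power 0.90, dropout 20%, 60 per arm. From section 5.3: a 95% interval. Assumed: true difference 0 for the sample size, equal SDs, normal approximation, and a range of true benefits, because the protocol projects none.

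**The plan's own figure.** For two one-sided tests at a true difference of 0:

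n = 2 × [SD × (z(1-α) + z(1-β/2)) / limit]²

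With α = 0.05 per side: 2 × [0.74 × (1.645 + 1.645) / 0.5]² = 47.4, so 48 per arm, and 48 / 0.8 = 60. The stated size reproduces. It corresponds to a 90% interval. With α = 0.025 per side, which matches the 95% interval in section 5.3, n = 56.9, so 57, or 72 after dropout. Both intervals are therefore carried through below.

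**Chance of each conclusion.** With n evaluable per arm, SE = 0.74 × √(2/n) and c = 0.5 - z × SE. For a true benefit d:

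- Equivalence: Φ((c - d)/SE) - Φ((-c - d)/SE)
- Upper 95% bound below +0.5: Φ((0.5 + d)/SE - 1.96)

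With n = 48, SE = 0.151; c = 0.204 (95% interval) or 0.252 (90% interval).

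| True benefit (PAI points) | Equivalence, 95% interval | Equivalence, 90% interval | Upper 95% bound below +0.5 |
|---|---|---|---|
| 0 | 82% | 90% | 91% |
| 0.1 | 73% | 83% | 98% |
| 0.2 | 51% | 63% | 99.6% |
| 0.25 | 38% | 50% | 99.9% |
| 0.3 | 26% | 37% | >99.9% |
| 0.4 | 10% | 16% | >99.9% |
| 0.5 | 2.5% | 5% | >99.9% |

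**Where failure becomes the likelier result.** The chance of equivalence falls to about one half when d reaches c: about 0.20 (95%) or 0.25 (90%) with 48 per arm. With all 60 evaluable, SE = 0.135 and c is 0.24 or 0.28. The chances are then 60% or 72% at a benefit of 0.2, and 32% or 43% at 0.3.

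**Chance of a result with no defined reading.** With 48 per arm and the 95% interval, this is 99.6% - 50.7% = 49% at a benefit of 0.2 and about 74% at 0.3.

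**Check on the approximation.** Simulation with t-based 95% intervals and 50 per arm (60/1.2) gives equivalence 83.5%, 51.3% and 26.6% at benefits of 0, 0.2 and 0.3. The upper bound is below +0.5 in 91.8%, 99.7% and nearly 100%.

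**Is the planned size enough for the added reading?** Non-inferiority at one-sided 0.025 with 90% power: 2 × [0.74 × (1.960 + 1.282) / 0.5]² = 46.0, taken up to 47; 47 / 0.8 = 58.75, so 59. The planned 60 covers it.

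**The case against.** The operative text is consistent. The abstract, design, hypothesis, sample size and primary analysis all say equivalence, and the research question has no direction. Section 2 is background and sets no decision rule, and showing similarity already satisfies half of similar or better. This stands: the plan contains no error of logic or arithmetic on this point.

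A reader might infer that any Reciproc protocol that heals better would usually fail the trial. The figures do not support that. A benefit of 0.1 passes 73% to 83% of the time and one of 0.2 passes 51% to 63% (48 per arm). Nor do the documents predict a benefit: sections 1.1 and 1.2 raise possible disadvantages, such as reduced irrigant action and debris extrusion. Part of the shortfall under the 95% interval also comes from the separate mismatch between sections 5.2.1 and 5.3, which is why both intervals are shown.

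A reader might also infer that a better result would be hidden. It would not. The interval shows direction, and success rate and change in periapical status have superiority tests. Those are not the primary outcome, however, so they supply no primary conclusion.

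Finally, the reading of each interval position is often left to a statistical analysis plan, which is not at hand. That weakens any charge of omission. What remains is that the protocol itself fixes the primary rule and keeps superiority testing for the other outcomes, while section 2 expressly contemplates a better result.

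**Conclusion.** The point holds as a cheap improvement to a coherent equivalence design. The rationale is one-directional, and the only primary conclusion defined is two-sided. For a true benefit above about 0.20 to 0.25 PAI points with 48 evaluable per arm (0.24 to 0.28 with no dropout), missing equivalence is the likelier result, although harm of 0.5 would be excluded almost always. Below that range the trial more often than not shows equivalence.

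The size rests on a symmetric limit, a common SD of 0.74, assumed benefits and a normal approximation. Section 5.3 names a Wilcoxon-based procedure on a five-level score, so the exact percentages may differ. A reader might conclude that the equivalence design is wrong or must be replaced by non-inferiority. The documents do not support that, because equivalence is the hypothesis they state throughout.

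**What to change.** Keep the equivalence test as primary. In sections 5.1 and 5.3, define the difference as SFSC minus HFLC, with higher PAI worse, and state that the same two-sided 95% confidence interval is read in this order:

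1. Upper bound below +0.5: SFSC is non-inferior.
2. Both bounds within ±0.5: also equivalent.
3. Upper bound below 0: also superior.

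Every reading that applies is reported. An interval of (-0.4, -0.1), for instance, is all three, and (-0.596, -0.004) is non-inferior and superior but not equivalent.

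With the 95% interval, non-inferiority and superiority each stay at one-sided 0.025. Any false reading requires the interval to miss the true difference, so no further adjustment is needed. With a 90% interval those two readings would be at one-sided 0.05, so the interval level should be stated explicitly. The added readings do not change the power for equivalence itself, which on the 95% interval is about 82% with 48 evaluable per arm.

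The cost is two or three sentences, with no extra patients, data or alpha. The downside is a graded primary conclusion in place of a single yes or no. The text should be fixed before the 12-month results are examined by arm.
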